### Age stratification

The study will analyse antibody concentrations and properties in children stratified into distinct age groups: 0 to < 2, 2 to < 5, 5 to < 10, and ≥ 10 years, as proposed by Cuevas et al. [21]. This stratification is crucial due to the differences and dynamics of the nature of TB disease across age. In the youngest age range (infants and children < 2 years old), disseminated diseases and heightened susceptibility to progression from TB infection to TB disease is well-documented [22]. The risks for progression from infection to disease, as well as the subsequent mortality risk following development of disease, consistently declines during childhood, reaching its lowest point between 5 and 10 years of age [23]. Transitioning into adolescence and the onset of puberty, typically beyond the age of 10 years, the phenotype of TB disease becomes more adult-like. Pulmonary TB becomes more prevalent during this phase, contributing to an upsurge in TB-related mortality rates [24, 25].

### Selected antigen targets and antibody properties for serological assay

Some previous studies in children have demonstrated improved specificities achieved by combining both protein and glycolipid antigens within serological assays [26–29]. Furthermore, several studies have illuminated the potential for heightened sensitivity through the combined analysis of multiple antigen targets, effectively overcoming the interindividual heterogeneity of the human humoral immune response to *M. tuberculosis* [26–33].

We will analyse antibodies concentrations and properties against single protein antigens, single glycolipid antigens [12, 34–40], as well as multiple antigens in combination (Table 2). The types of antigens include cell wall fractions, whole cell lysates, and total lipids of *M. tuberculosis*. The selection of protein antigens is based on results from large protein microarray studies in adults [41–46], one large multiplex bead-based study in children [31], and published and unpublished data from an adult study performed in the U.K (MIMIC study; personal communication [name]) [47]. In order to enhance specificity, the overlap of the antigen targets for *M. tuberculosis* with Bacillus Calmette-Guérin (BCG) and other non-tuberculous mycobacteria will be reduced.

**Table 2 Tab2:** Key protein, glycolipid, and multiple antigens

Type	Name	Rv number/Full name
Protein	**FbpC** (Ag85C)	Rv0129c
	**PstS3**	Rv0928
	**PstS1**	Rv0934
	**PapA4**	Rv1528
	**GarA**	Rv1827
	**Apa** (Mpt32)	Rv1860
	**FbpB** (Ag85B)	Rv1886c
	**Mpt63**	Rv1926c
	**Mpt64**	Rv1980c
	**HspX** (Acr)	Rv2031c
	**Acg**	Rv2032
	**Rv2034**	Rv2034
	**Hrp1**	Rv2626c
	**EsxO-EsxP**	Rv2346-Rv2347
	**EspA**	Rv3616c
	**FbpD** (Mpt51)	Rv3803c
	**FbpA** (Ag85A)	Rv3804c
	**EsxB** (CFP-10)	Rv3874
	**EsxA** (ESAT-6)	Rv3875
	**EsxA-EsxB** (ESAT6-CFP10)	Rv3875-Rv3874
	**EspD-EspC**	Rv3614-Rv3615
	**EspB**	RV3881c
	**Ag85 complex**	Rv3804c-Rv1886c-Rv0129c
Glycolipid	**LAM**	Lipoarabinomannan
	**PDIM**	Phthiocerol dimycocerosates
	**TDM**	Trehalose dimycolates
	**TMM**	Trehalose monomycolates
	**PGL**	Phenolic glycolipid
Multiple antigens (H37Rv)	**Cell wall fractions**	contains proteins and non-protein compounds such as mAGP of *M. tuberculosis*
	**Cell membrane fractions**	contains the cytoplasmic membrane and components of the outer lipid layer.
	**Whole cell lysates**	contains proteins, lipids and carbohydrates present within the *M. tuberculosis* bacterial cell
	**Total hypoxic lipids**	containing hypoxic culture *M. tuberculosis*
	**Total normoxic lipids**	containing normoxic culture *M. tuberculosis*

Abbreviations: Acg - alpha-crystallin homolog -coregulated gene; Acr - alpha-crystallin homolog; Ag85 complex - antigen 85 complex; Apa - alanine and proline rich secreted protein; CFP-10 - culture filtrate protein-10; ESAT-6 - early secreted antigenic target-6; EspA - ESX-1 secretion-associated protein A; EsxA/B/C/D/O/P - early secretory antigenic target homolog A/B/C/D/O/P; FbpA/B/C/D - fibronectin binding protein A/B/C/D; GarA - Glycogen accumulation regulator A; Hrp1 - hypoxic response protein 1; HspX - heat shock protein-X; Mpt32/51/63/64 - Proteins purified from Mycobacterium tuberculosis 32/51/63/64; PapA4 - polyketide synthase (PKS) associated protein; PstS1/3 - periplasmic phosphate-binding lipoprotein S1/3

Together with targeted *M. tuberculosis* antigens, this study will evaluate the following distinct properties of the antibodies: isotypes and their subclasses, FcR binding profiles, and antibody glycosylation patterns (refer to Fig. 1). The rational for this is to obtain further information about the immune response to the antigen. TB disease results from a combination of the mycobacteria infecting and the resulting pathologic immune response. Therefore, antibody concentrations may only reflect on exposure, timepoint, and burden of mycobacteria, whereas additional properties such as FcR may reflect on the fact if the immune response producing tissue damage and pathology or not. This is shown in studies in children with TB disease that have demonstrated the potential enhancement of serological assay sensitivity through the integration of diverse antibody isotypes [48–50]. Recent advancements in adult research have indicated that an evaluation of certain antibody properties, such as FcRs binding profiles and glycosylation patterns, could potentially enable the differentiation between TB disease and infection [12, 13].

**Fig. 1 Fig1:**
[figure not shown]
Overview of the antibody properties Interaction between the surface of *M. tuberculosis*, binding of the antibody and the recognition of the antibody by an immune cell. Sections **A**, **B**, and **C** detail the different antibody properties: **A**) antibody isotypes and IgG subclasses **B**) glycosylation patterns of antibodies, including a core glycan and potential additional sugar residues (1–4) **C**) activating and inhibiting FcRs with varying affinities for antibody binding Abbreviations: Mtb -Mycobacterium tuberculosis; FcR -fragmented crystallizable region (Fc) receptor; IgM - immunoglobulin M; IgD - immunoglobulin D, IgG_1 − 4_ - immunoglobulin G_1 − 4_; IgA - immunoglobulin A, N - N-acetylglucosamine; M - mannose; G - galactose; S - sialic acid; F - fucose

As a quality control and potential normalisation variable, we will measure the total antibody concentration of each isotype and the total antibody concentration binding to distinct FcRs.

### Sample preparation

Upon plasma sample collection, preservation is ensured through storage in a − 80 °C freezer until the initiation of laboratory assays. Customised multiplex antigen-coupled beads will be produced to evaluate antigen-specific antibodies concentrations and properties in plasma samples. The protein antigens will be coupled to carboxylated beads through covalent NHS-ester linkages, using 1-ethyl-3-(3-dimethylaminopropyl) carbodiimide hydrochloride and Sulfo-NHS (Thermo Scientific), following the manufacturer’s recommendations [51, 52]. Glycan antigen LAM, single lipid antigens (e.g., TDM and TMM), and multiple lipid antigen from *Mycobacterium tuberculosis* total lipids will be modified using 4-(4,6-dimethoxy [1, 3, 5] triazin-2-yl)-4-methyl-morpholinium (DMTMM) dissolved in ethanol and conjugated beads following the COOH-DMTMM method [53].

The antigen-specific antibodies concentrations and properties will be measured using different PE-labelled detection antibodies as follows: for the isotypes and subclasses, PE-coupled detection antibodies (anti-IgG, anti-IgA, anti-IgM, anti-IgG_1_, anti-IgG_2_, anti-IgG_3_ and anti-IgG_4_) at a concentration of 1 µg/mL; [52] for the FcR binding profiles, FcRs (FcγRIIIa/CD16a, FcγRIIIb/CD16b, FcγRIIa/CD32a H167, FcγRIIb/CD32b, FcγRI/CD64 from R&D Systems) will be labelled with PE and added to the samples at a concentration of 1 µg/mL; and for the glycosylation profiles, PE-labelled lectins (SNA for sialic acid, ECL for galactose, LCA for fucose and PHA-E for N-acetylglucosamine) will be used at a concentration of 20 µg/mL. After 2 h of incubation at room temperature, the beads will be washed with PBS-0.05% Tween20, and PE signal will be measured using xMAP technology. (refer to Fig. 2)

**Fig. 2 Fig2:**
[figure not shown]
Multiplex bead-based serological assay For the multiplex bead-base serological assay (1) specific antigens are coupled to beads, (2) plasma samples are incubated with the antigen-coupled beads, allowing specific antibodies to bind to corresponding antigens, (3) fluorescently labelled detection antibodies are added, binding to antigen-specific antibodies or their properties, (4) fluorescence is measured by using a coloured laser, and concentrations are then calculated based on a standard curve

### Data management

All data will be securely entered and shared through password-protected and encrypted systems to uphold the confidentiality of health-related personal information. Adhering to Swiss legal requirements for data protection (Ordinance HRO Art. 5), our procedures for storing biological samples and handling health data are meticulously governed. Coding mechanisms and personalised logins are implemented to grant exclusive access to the study database and source documents for authorised personnel, thereby preventing third-party disclosure. Unique identification numbers are assigned to the biological samples and health-related personal data.

### Data analysis

Descriptive statistics, including mean, median, standard deviation, and interquartile range, will be used to summarise antibody concentrations stratified by diagnostic group (TB disease, TB infection, healthy TB-exposed controls, and non-TB lower respiratory tract infections) and age groups (< 2 years, 2 to < 5 years, 5 to < 10 years, and ≥ 10 years). Antigen-specific antibody concentrations will be analysed in relation to the total (nonspecific) antibody concentrations. Comparisons between groups will be made using t-tests or Mann-Whitney *U* tests if normality assumptions are not met. Children with TB disease and infection will be compared with the following groups: all other remaining children combined, healthy TB-exposed children, and children with non-TB lower respiratory tract infections.

To assess the performance of each individual antigen specific antibody feature as a diagnostic assay, sensitivity and specificity will be calculated based on cut-off values determined by the highest Youden’s index. Receiver operating characteristic (ROC) analysis will be performed, and area under the curve (AUC) will be calculated (confidence interval will be determined using the DeLong method).

In subsequent analyses, we aim to evaluate the combined interpretation of antigen-specific antibodies concentrations and properties using different strategies:

Strategy one involves defining cut-off values based on a specificity of ≥ 98%, in accordance with the minimal WHO’s target product profile(TPP) requirement for a biomarker-based detection test. We will calculate the corresponding sensitivity. Similarly, we will determine cut-off values based on a sensitivity of ≥ 66% and calculate the corresponding specificity. To assess the combined interpretation of multiple antigen targets, the test for a specific antibody or antibody property will be scored positive if at least one antibody level against a specific antigen exceeds the cut-off value in an individual’s plasma sample, and negative if all antibody levels against all antigens in a plasma sample are below the cut-off values.

Another strategy for the combined interpretation of multiple antibody concentrations and properties will involve feature selection using the least absolute shrinkage and selection operator (LASSO). This approach will help identifying the most informative features that could be used in diagnostic assays. To validate the predictive power of the selected features (k features), we will train and evaluate an additional model using only those k features. In a further step, we will include the selection of antibody concentrations and properties in the training of the model. By performing feature selection using LASSO, we aim to maximize prediction performance using all features and select the k most informative features after the training stage. This procedure is based on the concept that selecting the most informative features from a well-performing prediction model will also yield a well-performing prediction model when one only has access to the selected subset of features. Recent advances in machine learning research will enable us to incorporate feature subset selection directly into the training step of a model [54, 55]. Therefore, we optimise not only the prediction performance but also the subset selection of k features during training. The choice of subset size, k, should be based on external constraints. The diverse sensitivities and specificities observed in paediatric TB serological tests make a precise sample size determination challenging. To estimate the sample size for our experiments, we used data generated from a cohort of adults with latent infection (*n* = 20) and active pulmonary disease (*n* = 22) from South Africa [56]. For the analysis of 75 antibody features, linear regression was conducted to assess the association between diagnosis and antibody feature, while controlling for age and gender. For the thirteen features exceeding a false discovery rate threshold of 10%, the partial correlation coefficient of 0.50 or higher was observed between diagnosis and antibody feature. Using this estimate as the effect size of biologically active antibody features, 68 individuals in an independent cohort (34 LTB, 34 ATB) would provide a statistical power of 80% to observe significant differences in top antibody features between tuberculosis infection and disease at an alpha level of 0.0005. This alpha level represents the threshold for significance required by the Bonferroni-Holm correction method, set at 0.0005 to accommodate the testing of 100 antibody features.

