CITRUS is a multicentric prospective diagnostic study done at nine centres across Switzerland (Bern, Basel, Zurich, Lausanne, Geneva, Aarau, St. Gallen, Lucerne, Bellinzona). Its primary objective is to evaluate and validate novel immunodiagnostic assays for childhood TB [14, 15]. The study includes children under the age of 18 years, with or without a history of Bacillus Calmette-Guérin (BCG) vaccination, who are undergoing evaluation for TB disease, infection, and exposure. Children who have received any anti-mycobacterial treatment for five days or more before inclusion or who have been previously treated for TB disease or infection are excluded. Recruitment for the CITRUS study began in May 2017 and is currently ongoing.

PTBred is a multidisciplinary collaborative network established in 2014 in Spain, recruiting children < 18 years with TB. Since 2017, different types of samples have been stored in the Biobank of the Gregorio Marañon Hospital or in the individual collection registered as C.0006631 in the National Biobank Collections Registry. For this study, a common protocol for sample processing was implemented in October 2019, including children with children with TB disease, infection, and exposure irrespective of their BCG-vaccination status. The pTBred and CITRUS study follow the same inclusion and exclusion criteria [16].

The ProPAED study collected samples from children and adolescents presenting with fever and cough at two emergency departments in Switzerland (Basel and Aarau), from January 2009 to February 2010. For the ProPAED study, children with severe immunocompromise or known HIV infection, those undergoing immunosuppressive treatment, children with *M. tuberculosis* infection, neutropenia, cystic fibrosis, viral laryngotracheitis, hospital stay within the preceding 14 days, or other severe infections (e.g., osteomyelitis, endocarditis, or deep tissue abscesses) were excluded [17].

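### The sample size rests on an age- and sex-adjusted regression, but the group tests and ROC analyses are planned unadjusted, and the four age groups have no defined place in the inference

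*Protocol article*

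**What the plan says.** Three parts of the protocol article bear on this.

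- **Data analysis, group tests.** "Comparisons between groups will be made using t-tests or Mann-Whitney" U tests, the latter when normality fails. Sensitivity, specificity and AUC are then computed for each feature. No age, sex or BCG term is named. The only adjustment mentioned is relating antigen-specific to total antibody concentration. The four age groups appear here only in the sentence on descriptive summaries.
- **Data analysis, sample size.** The pilot was "a cohort of adults with latent infection" (20) and active pulmonary disease (22). In it, "linear regression was conducted to assess the association between diagnosis and antibody feature, while controlling for age and gender". For the features that passed the false discovery threshold, "the partial correlation coefficient of 0.50 or higher was observed between diagnosis and antibody feature". From this the plan derives "68 individuals in an independent cohort (34 LTB, 34 ATB") for 80% power at alpha 0.0005, which is 0.05 divided by 100 features.
- **Age stratification.** "The study will analyse antibody concentrations and properties in children stratified into distinct age groups": under 2, 2 to under 5, 5 to under 10, and 10 years or more. The section calls this crucial, and the Discussion lists an age-stratified data analysis among the study's features.

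Under Study setting and population, CITRUS enrols children "with or without a history of Bacillus Calmette-Guérin (BCG) vaccination", and pTBred likewise enrols regardless of BCG status.

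**The concern.** The test that is written down is not the one behind the power figure. The effect size is an association with age and sex already removed, while the planned tests and ROC curves leave both in.

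This matters because the protocol itself argues that age changes the disease. The diagnostic groups also reach the study by different routes: evaluation for TB exposure, infection or disease in CITRUS and pTBred, and presentation with fever and cough at emergency departments in ProPAED. The design as described does not match them on age. If the groups differ in age and a marker varies with age, a marker with no diagnostic value can show a small p-value, a raised AUC and a cut-off that partly detects age. BCG history could act in the same way, since the protocol acknowledges cross-reactivity.

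The age groups do not settle the matter as written. The text does not say whether tests are pooled over the strata, run within them or combined across them.

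**Working it through.** **Inputs from the protocol:** partial r = 0.50; 34 + 34 = 68 children; alpha = 0.0005; four age groups. Sidedness is not stated. Two-sided is assumed because it reproduces the plan's figure best; z(1 − 0.00025) = 3.481.

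**1. The plan's own figure.** Fisher z for a partial correlation with k covariates: power = Φ(√(N − 3 − k) · atanh(r) − 3.481), where atanh(0.50) = 0.5493.
- With k = 2 (age, gender) and N = 68: √63 × 0.5493 = 4.360, and Φ(4.360 − 3.481) = **0.81**. The N for 80% is 67, or 68 for equal groups. The stated figure reproduces as an adjusted analysis.

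**2. The written test on all 68, with no age imbalance.** The equivalent standardised difference is d = 2r/√(1 − r²) = 1.155. If age and sex explain a share R² of the within-group variance (assumed), the unadjusted difference is d√(1 − R²). Two-sample noncentral t at alpha 0.0005, 34 versus 34:

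| R² (assumed) | d | Power | Per group for 80% |
|---|---|---|---|
| 0 | 1.155 | 0.86 | 32 |
| 0.10 | 1.095 | 0.80 | 35 |
| 0.20 | 1.033 | 0.72 | 39 |
| 0.30 | 0.966 | 0.63 | 44 |

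Simulated Mann-Whitney power at R² = 0 is 0.81.

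**3. Pooled unadjusted test with an age imbalance and no true difference.** The spurious shift in SD units is (within-group correlation of marker with age) × (age gap in SD). For example, 0.4 × 0.8 = 0.32. The AUC of the null marker is Φ(shift/√2). All shifts are assumed; 34 versus 34, t-test:

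| Shift (SD) | AUC | Rejection at 0.05 | Rejection at 0.0005 |
|---|---|---|---|
| 0.10 | 0.53 | 7% | 0.1% |
| 0.32 | 0.59 | 26% | 1.3% |
| 0.50 | 0.64 | 53% | 6.5% |

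**4. Separate tests within four strata.** An even split of the 68 (assumed) gives 34/4 = 8.5, so 8 to 9 per group. With d = 1.155 at alpha 0.0005, t-test power is 0.052 (8 versus 8), 0.061 (8 versus 9) and 0.072 (9 versus 9). Simulated Mann-Whitney power is 0.03 to 0.06.

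**5. One adjusted model on all 68.** Three age-group indicators plus sex give k = 4.
- Fisher z: √61 × 0.5493 = 4.290, and Φ(4.290 − 3.481) = **0.79**.
- Noncentral F, with f² = 0.25/0.75 = 1/3 on 62 error degrees of freedom: **0.80 to 0.85**, depending on the convention for the noncentrality parameter.

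**The case against.** The best defence is that the mismatch may cost little. On all 68 the unadjusted t-test has power 0.86, and still 0.80 if age and sex explain 10% of the variance. That stands: the unadjusted test falls clearly short of 80% only if they explain more than about 10%, and the protocol neither supports nor excludes this. The adult pilot, as reported, gives no guide for children.

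A reader might infer that the results must be either age-confounded or nearly powerless. The documents do not support this, for four reasons.

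- The choice is not forced. An adjusted model, or a test combined over strata, avoids both problems (step 5).
- Testing within strata is not stated. The Data analysis section ties the age groups only to descriptive summaries, and the remarks elsewhere are general.
- The 8 to 9 children per group come from dividing 34 by four. The 68 is what one contrast needs, not the number of samples available, which is not given. Nor is significance at 0.0005 arithmetically out of reach at that size: with 8 versus 9, the smallest exact two-sided Mann-Whitney p is 2/C(17,8) = 2/24310 = 0.00008.
- Confounding is not shown. No age or BCG distribution by group is given. Relating signals to total antibody, and choosing antigens with less BCG overlap, may remove part of it.

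One could also say that an article may leave covariates to an analysis plan. But this article does name its tests, and they differ from the model used for its own power.

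**Conclusion.** The point holds as a mismatch in the text. The power belongs to an analysis adjusted for age and sex, the stated tests and ROC analyses are unadjusted, and the age groups that the protocol calls crucial enter neither the sample size nor alpha.

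The main consequence is a risk of age confounding in the pooled comparisons. Its size depends on assumed shifts of 0.1 to 0.5 SD, and ranges from negligible to severe. A loss of power in the pooled test is possible but not established. The 5% to 7% power within strata applies only if tests are run separately, at alpha 0.0005, on an even split of the 68.

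Confidence is high for the mismatch and conditional for its consequences. The change is worth making because the better analysis is already in the document, as the basis of the sample size.

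**What to change.** - Make the primary group comparison a regression of the suitably transformed antibody signal on diagnosis, with age and sex. Age may be continuous or the protocol's four groups; continuous age leaves less residual confounding within the wide bands.
- Add BCG status where it is recorded. Add cohort only for contrasts within CITRUS and pTBred. The non-TB respiratory controls come from ProPAED alone, so a cohort term cannot be separated from diagnosis there, and this limit should be stated.
- Report an age-adjusted AUC beside the crude one.
- Say that results within age strata are descriptive.
- Restate the power for the model finally chosen.

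The cost is wording, slightly more analysis and a few degrees of freedom: about 79% to 85% power with all 68, provided that the partial correlation given age group and sex is 0.50. Age is already needed for the stratification. Sex and BCG history are assumed to be on record.

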## Methods

### Aim

The aim of this study is to evaluate the diagnostic performance of serological assays in detecting children with TB disease, and in distinguishing those subjects from (1) healthy TB-exposed children, (2) children with non-TB lower respiratory tract infection, and (3) children with TB infection.

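### The listed group comparisons omit TB disease versus TB infection, which is the third aim and the only powered contrast, and leave the index group unclear

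*Protocol article*

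**What the plan says.** **Aim (Methods, repeated in the Abstract).** The assays are to detect children with TB disease, "distinguishing those subjects from (1) healthy TB-exposed children, (2) children with non-TB lower respiratory tract infection, and (3) children with TB infection". Disease alone is the target condition, and infection is the third comparator.

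**Data analysis, group comparisons.** After naming the t-test and the Mann-Whitney test, the protocol states: "Children with TB disease and infection will be compared with the following groups: all other remaining children combined, healthy TB-exposed children". The non-TB LRTI group completes the list. Infection is on the index side and is not a comparator in its own right.

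**Data analysis, sample size.** The only calculation states that "68 individuals in an independent cohort (34 LTB, 34 ATB) would provide a statistical power of 80" per cent "to observe significant differences in top antibody features between tuberculosis infection and disease at an alpha level of 0.0005". The effect size comes from adult data in which "the partial correlation coefficient of 0.50 or higher was observed between diagnosis and antibody feature".

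**Data analysis, performance measures.** The text on Youden cut-offs, ROC curves, the fixed specificity and sensitivity cut-offs, and LASSO names neither a case group nor a control group.

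**The concern.** The aim, the comparison list and the sample size should describe the same contrasts, and they do not. The aim and the sample size both require disease versus infection; the comparison list leaves it out.

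What is at stake is who counts as a case. Under Case definitions, infection means a positive TST or IGRA without disease, and healthy exposed children are negative on those tests. If infected children count as cases against exposed children, the comparison partly reproduces the TST/IGRA classification. The Background says those tests are not well suited to screening for disease. The protocol also justifies measuring Fc receptor binding and glycosylation by their possible ability to separate disease from infection, which is the contrast left off the list.

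**Working it through.** **1. Aims against listed comparisons, on both readings**

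| Contrast in the aim | Listed if disease and infection are pooled? | Listed if each is compared in turn? |
|---|---|---|
| Disease vs healthy exposed (aim 1) | No: cases include infection | Yes |
| Disease vs non-TB LRTI (aim 2) | No: cases include infection | Yes |
| Disease vs infection (aim 3, the powered contrast) | No | No: infection appears only inside the combined group |

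The pooled reading fits the list well: removing disease and infection from the four diagnostic groups leaves exactly the two comparators named, listed first combined and then singly. The in-turn reading is also possible. It makes the combined group change its content: for disease it is infection + exposed + LRTI, and for infection it is disease + exposed + LRTI. Aim 3 is unlisted either way.

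**2. The protocol's own sample size**

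Inputs from the sample-size text: partial correlation r = 0.50, alpha = 0.05/100 = 0.0005, power 80%, and two covariates (age and gender). Sidedness is not stated; two-sided is assumed.

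Fisher z: N = ((z for 1 − alpha/2 + z for power) / atanh(r))² + 3 + covariates

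- N = ((3.481 + 0.842) / 0.549)² + 3 + 2 = 66.9, so 34 + 34 = 68 when rounded up to equal groups.
- Power at N = 68 is 81.0%.
- With no covariates, N = 64.9 and power at 68 is 82.8%.

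The figure of 68 reproduces, and it belongs to disease versus infection. Listing that contrast leaves it unchanged.

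**3. What pooling could cost (illustration only)**

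Assumptions not in the protocol: the feature is shifted by the planning effect in disease only, infected children have the same distribution as controls, and disease makes up a share p of the pooled cases.

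- d = 2r/√(1 − r²) = 1.00/√0.75 = 1.155.
- Undiluted AUC = Φ(1.155/√2) = 0.793.
- Pooled AUC = p × 0.793 + (1 − p) × 0.50. At p = 0.5 this is 0.646. At p = 0.25 it is 0.573, and at p = 0.75 it is 0.720.
- Pooled mean difference at p = 0.5 is 0.5 × 1.155 = 0.577. The variance in the pooled cases is 1 + p(1 − p)d² = 1.333, so the average SD is √((1 + 1.333)/2) = 1.080.

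Power at alpha 0.0005, two-sided, by the normal two-means formula:

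| Comparison | Power |
|---|---|
| Undiluted, 34 vs 34 | about 90% |
| p = 0.5, 34 vs 34 | about 10% |
| p = 0.5, 68 vs 68 | about 36% |
| p = 0.25, 34 vs 34 | about 1% |
| p = 0.75, 34 vs 34 | about 45% |

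The 90% here and the 81% in step 2 come from different formulas for the same effect, so power should be compared only within the table.

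**The case against.** The best defence is that the sentence is loosely worded and the intent is clear elsewhere.

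- **Pooling is not certain.** The same paragraph has just set out four separate diagnostic groups, and the sentence may mean each group in turn. This stands: a reader might infer that disease and infection will be merged as cases, but the text does not settle it. On the in-turn reading, aims 1 and 2 are covered.
- **The sentence governs the hypothesis tests.** It follows the t-test and Mann-Whitney text, and nothing carries a pooled case group into the ROC or LASSO analyses. This also stands, so it cannot be said that the study as a whole will estimate sensitisation rather than disease. But those analyses name no contrast, so they do not supply the missing one.
- **The intent to test disease against infection is on the page.** The Aim names it, the sample size is built on it, and the descriptive summaries keep the two groups apart. A reader might therefore go too far in inferring that aim 3 will have no result. What is missing is its entry in the list of comparisons.
- **Infection has a legitimate place on the index side.** The Background and Discussion present serology as a tool for both infection and disease. That justifies an additional comparison, but not leaving out one of the stated aims.
- **The loss under pooling is hypothetical.** It rests on an assumed case mix and feature pattern, and it transfers an effect estimated for disease versus infection to disease versus exposed. This is correct, and the finding does not depend on it.

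None of these points puts disease versus infection on the list. An unseen analysis plan might add it, but the published sentence would still conflict with the aim and the sample size.

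**Conclusion.** Wrong as written. The comparison sentence contradicts the Aim and the sample-size calculation, because it omits disease versus infection on either reading. That conclusion comes from the text alone and needs no numerical assumption. The second fault is ambiguity: pooled, the list answers none of the three aims; in turn, it answers two of the three and uses a combined comparator whose content changes with the index group.

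The documents do not support inferring an error in the sample size, which reproduces. Nor do they establish a fall in AUC from 0.79 to 0.65: that is an illustration under pooling, with equal numbers of disease and infection and infected children who resemble exposed children.

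**What to change.** Reword the comparison sentence in the Data analysis section so that TB disease alone is the index group, compared separately with healthy TB-exposed children, children with non-TB LRTI and children with TB infection. State that the ROC and cut-off analyses use these same three contrasts. If infection versus uninfected children, or disease versus all others combined, is also wanted, list each separately and define which groups make up its comparator.

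The cost is a few sentences of wording. No new samples or data are needed, and the 34 + 34 calculation stays as it is.
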